#### 3.4.1. Symptoms/Signs Unrelated to Study Drug

If unacceptable symptoms or signs of toxicity are considered unrelated to study drug and resolve within 21 days, the subject may resume study treatment at his or her current dose level.

If unacceptable symptoms or signs of toxicity are considered unrelated to GSK1363089 but have not resolved to Grade  $\leq 1$  or to within 10% of baseline values within 21 days, the subject will receive no further doses of GSK1363089 and will enter the Post-Treatment Period.

#### 3.4.2. Symptoms/Signs Related to Study Drug

If unacceptable study drug-related symptoms resolve within 21 days, the subject may resume study treatment with a reduction in dose.

If, after 21 days, study drug-related symptoms or signs of toxicity do not resolve to Grade  $\leq 1$  or to within 10% of baseline values, the subject will receive no further doses of GSK1363089 and will enter the Post-Treatment Period.

#### **3.4.3. Dose Reduction in Cohort 1 (Intermittent 5&9 Dosing)**

In Cohort 1, GSK1363089 will be dosed at 240 mg/day on an Intermittent 5&9 dosing schedule. If a single dose reduction is required, the reduction will be to 160 mg/day; if a second dose reduction is required, the reduction will be to 100 mg/day. If a subject requires dose reduction more than 2 times because of unacceptable study drug-related AEs, the subject's continuation on the study must be discussed with and agreed to by the GSK study physician.

#### **3.4.4. Dose Reduction in Cohort 2 (Daily Dosing)**

In Cohort 2, GSK1363089 will be dosed at 80 mg/day on a daily dosing schedule. If a single dose reduction is required, the reduction will be to 60 mg/day. If toxicities occur while on the 60 mg/day dosing schedule, further modifications to the schedule will depend on how long the subject has been on 60 mg/day dosing, as follows:

- If toxicities occur after 3 or more weeks on 60 mg/day dosing, then a 1 week treatment rest should be instituted, such that a new schedule of 3 weeks on/1 week off is implemented. If 60 mg/day dosing is still not tolerable on the 3 week on / 1 week off schedule, the subject's continuation on the study, in addition to any further modifications to the dosing schedule, must be discussed with and agreed to by the GSK study physician.
- If toxicities occur after less than 3 weeks on 60 mg/day dosing, the subject's continuation on the study, in addition to any further modifications to the dosing schedule, must be discussed with and agreed to by the GSK study physician.

#### **3.5. Requirement for Collection of Paired Tumor Biopsies**

Following the implementation of protocol Amendment 4.0, the collection of fresh, paired tumor biopsies will become a requirement rather than an option, to allow the assessment of the expression of pharmacodynamic markers of GSK1363089 activity, in particular relating to the c-MET pathway (e.g. total c-MET, phospho-MET and downstream markers).

After the first 6 subjects have been enrolled under Amendment 4.0 and have had paired tumor biopsies collected, enrolment will be put on temporary hold, while the safety and acceptability of collecting paired biopsies, plus the pharmacodynamic data, are reviewed

by GSK. If there are no safety concerns, and the pharmacodynamic objective with respect to c-MET has not been met, then subject enrolment will recommence and continue until the target number of subjects for Cohort 2 has been reached.

The safety and pharmacodynamic data for the paired tumor biopsies will continue to be reviewed on an ongoing basis. If a safety concern with obtaining the biopsies should ever arise and/or the pharmacodynamic objective with respect to c-MET has been met, then paired biopsies will no longer be required in this study. This will be communicated to the sites and IRBs by letter from GSK or its designee.

If any subject is not able to provide the second biopsy (i.e. at Day 5-8), then that subject will be allowed to continue on study and will be eligible for inclusion in the safety and efficacy assessments. However, if by so doing, this would prevent at least 12 subjects being enrolled who do provide paired biopsies, then an extra subject will be enrolled.

Instructions for the collection of paired tumor biopsies are provided in Section 5.9.2 and the Pharmacodynamic Laboratory Manual.

## **4. STUDY POPULATION**

### **4.1. Target Population**

This study will be conducted in subjects with metastatic gastric carcinoma.

### **4.2. Inclusion Criteria**

A subject must meet the following criteria to be eligible for the study:

1. The subject has a histologically confirmed diagnosis of advanced or metastatic gastric carcinoma, or adenocarcinoma of the gastroesophageal junction or of the distal esophagus. Subjects with tumors of the gastroesophageal junction or of the distal esophagus may be eligible provided that the tumor is not of squamous or sarcomatous histology.
2. The subject has measurable disease, defined as at least one lesion that can be accurately measured in at least one dimension (longest diameter to be recorded) as  $\geq 20$  mm with conventional techniques or as  $\geq 10$  mm with spiral computerized tomography (CT) scan.

3. Ten unstained slides of representative tumor tissue or a paraffin block of tumor, archival or recently-prepared, have been identified for shipment to the central analysis laboratory. These samples will be used initially for determining the *c-MET*-amplification status by FISH.
4. The subject consents to provide paired tumor biopsies, directly prior to commencing study treatment and then between Days 5 and 8. These samples will be used for analysis of pharmacodynamic markers of GSK1363089 activity; they are in addition to the tumor tissue described in Inclusion Criterion 3.
5. The subject is at least 18 years old.
6. The subject has an ECOG performance status  $\leq 2$ .
7. The subject is able to ingest the GSK1363089 capsules.
8. In the adrenocorticotrophic hormone (ACTH) stimulation test, the subject has a serum cortisol level  $\geq 20$   $\mu\text{g/dL}$  (552 nmol/L) 30-90 minutes after injection of ACTH.
9. The subject has organ and marrow function as follows: absolute neutrophil count (ANC)  $\geq 1500/\text{mm}^3$ , platelets  $\geq 100,000/\text{mm}^3$ , hemoglobin  $\geq 9$  g/dL, bilirubin  $\leq 1.5$  mg/dL or  $\leq 1.5 \times \text{ULN}$  if no liver involvement (or  $\leq 2$  mg/dL or  $\leq 2 \times \text{ULN}$  with liver involvement); serum creatinine  $\leq 1.5$  mg/dL or calculated creatinine clearance  $\geq 60$  mL/min, ALT and AST  $\leq 2.5 \times \text{ULN}$  if no liver involvement or  $\leq 5 \times \text{ULN}$  with liver involvement.
10. The subject is capable of understanding and complying with the protocol and has signed the informed consent document.
11. Sexually active subjects (male and female) must use a medically-accepted method of contraception during the course of the study.
12. Female subjects of childbearing potential must have a negative serum pregnancy test at screening.
13. The subject has had no other diagnosis of malignancy (unless non-melanoma skin cancer or a malignancy diagnosed  $\geq 5$  years ago, and has no evidence of disease for 5 years prior to the screening for this study).
14. The subject has a QTcB (Bazett corrected) or QTcF (Frederica corrected)  $< 470$  msec. If the first ECG reading is  $\geq 470$  msec, repeat the ECG twice over a 10 minute period. Then use the average QTc value to determine whether the subject can be included.

### 4.3. Exclusion Criteria

A subject who meets any of the following criteria is ineligible for the study:

1. The subject has received more than two lines of prior cytotoxic chemotherapy for locally advanced or metastatic disease. For the purpose of this protocol, neoadjuvant therapy would not be considered to be prior cytotoxic chemotherapy. In addition, potential subjects who have received prior treatment with c-MET signaling inhibitor (e.g. Small molecule c-MET inhibitors and/or antibodies against HGF) are excluded.
2. The subject has received an investigational drug within 14 days of the first dose of study drug.
3. The subject has received chemotherapy, immunotherapy, or radiation therapy (to  $\geq 25\%$  of his or her bone marrow) within 14 days or has received nitrosoureas or mitomycin C within 6 weeks prior to the scheduled first dose of GSK1363089.
4. The subject has AEs due to investigational drugs or other medications administered more than 21 days prior to enrollment that have not recovered to Grade  $\leq 1$  using NCI CTCAE v3.0, with the exception of alopecia greater than grade 1.
5. The subject has known brain metastases.
6. The subject has uncontrolled intercurrent illness including, but not limited to, ongoing or active infection, symptomatic congestive heart failure, unstable angina pectoris, cardiac arrhythmia, or psychiatric illness/social situations that would limit compliance with study requirements.
7. The subject is pregnant or breastfeeding.
8. The subject is known to be positive for the human immunodeficiency virus (HIV).
9. The subject has a previously identified allergy or hypersensitivity to components of the GSK1363089 formulation.
10. The subject is unable or unwilling to abide by the study protocol or cooperate fully with the investigator or designee.

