### **Exclusion Criteria**

A subject who meets any of the following criteria is ineligible for the study:

1. The subject has received more than two lines of prior cytotoxic chemotherapy for locally advanced or metastatic disease. For the purpose of this protocol, neoadjuvant therapy would not be considered to be prior cytotoxic chemotherapy. In addition, potential subjects who have received prior treatment with a MET signaling inhibitor (e.g. Small molecule MET inhibitors and/or antibodies against HGF) are excluded.
2. The subject has received an investigational drug within 14 days of the first dose of study drug.
3. The subject has received chemotherapy, immunotherapy, or radiation therapy (to  $\geq 25\%$  of his or her bone marrow) within 14 days or has received nitrosoureas or mitomycin C within 6 weeks prior to the scheduled first dose of GSK1363089.
4. The subject has adverse events (AEs) due to investigational drugs or anti-cancer therapy administered more than 21 days prior to enrollment that have not recovered

to Grade  $\leq 1$  using National Cancer Institute (NCI) Common Terminology Criteria for Adverse Events (CTCAE) v3.0, with the exception of alopecia greater than grade 1.

5. The subject has known brain metastases.
6. The subject has uncontrolled intercurrent illness including, but not limited to, ongoing or active infection, symptomatic congestive heart failure, unstable angina pectoris, cardiac arrhythmia, or psychiatric illness/social situations that would limit compliance with study requirements.
7. The subject is pregnant or breastfeeding.
8. The subject is known to be positive for the human immunodeficiency virus (HIV).
9. The subject has a previously identified allergy or hypersensitivity to components of the GSK1363089 formulation.
10. The subject is unable or unwilling to abide by the study protocol or cooperate fully with the investigator or designee.

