##### **3.1.1. Pre-Treatment Period**

Subjects will undergo evaluations to determine study eligibility. Screening will be conducted within 28 days before initial treatment on Day 1. The following baseline evaluations must be done within 72 hours of the initial treatment: physical examination, measurement of vital signs, the Eastern Cooperative Oncology Group (ECOG) performance status (Appendix B), hematology, serum chemistry panel, urinalysis, and a pregnancy test (in women of childbearing potential). In addition, the appropriate arrangements must be made to ensure that 10 unstained slides or a paraffin block of archived tumor tissue are shipped to the central analysis laboratory, no later than 14 days after the subject's first dose of study drug.

It is important to note that in the event that enrolment of 30 evaluable subjects in Cohort 2 is completed before the target of 4 subjects with *c-MET* amplification, as defined by  $\geq 2$  copies of *c-MET* per copy of chromosome 7 (see Section 3.3.1 for full definition), has been reached, then extra subjects, with proven *c-MET* amplification, pre-screened by FISH, will be enrolled in the study, until the target is reached. In this instance, 10 unstained slides or a paraffin block of tumor tissue must be shipped to the central analysis laboratory as soon as possible after the subject signs the consent form. The subject will not be able to start the study treatment period until FISH results are available, and then only if they have *c-MET*-amplified tumor, as defined by  $\geq 2$  copies of *c-MET* per copy of chromosome 7.

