### **5.9.2. Fresh Frozen Tumor Tissue - Paired Tumor Biopsies**

The collection of paired tumor biopsies is required for all subjects who are enrolled in Cohort 2 after the implementation of Protocol Amendment 4.0. These samples will be used to study the effect of GSK1363089 on the expression of pharmacodynamic markers (e.g. total c-MET, phospho-MET and downstream markers).

Detailed instructions for sample preparation will be provided in the Pharmacodynamic Laboratory Manual and kits provided to the sites. The key points are summarized below:

- The baseline tumor biopsy should be collected as soon as possible prior to commencing study treatment, after all other inclusion and exclusion criteria are met, and at least 14 days after the completion of any prior anti-cancer therapy.
- The second tumor biopsy should be collected as close to Day 5 as possible, although it is acceptable to collect it up to Day 8 (Appendix B). It is important that the second tumor biopsy be obtained from the same organ as the pre-treatment biopsy, if at all possible.

Subjects should undergo core biopsies of either the primary gastroesophageal tumor or site of metastasis. The biopsies may be performed percutaneously under imaging guidance, or endoscopically, according to institutional practice. When endoscopic biopsies are performed we recommend at least 5-6 core biopsies with Jumbo forceps to ensure adequate yield of tissue. For the imaging-guided biopsies, 1-2 core biopsies will be performed with a 16-18-gauge needle. We recommend discussion of the feasibility of core biopsies with the radiologist/endoscopist performing the procedure to ensure that core biopsies can be indeed be performed.

Fine needle aspiration must not be used, as it would provide insufficient tumor tissue for studying the effect of GSK1363089 on the expression of pharmacodynamic markers.

All biopsies must be immediately embedded in OCT and snap frozen at -80 °C, in accordance with instructions in the Pharmacodynamic Laboratory Manual. It is highly recommended that a cytopathologist/pathologist be present during the tissue procurement procedures to ensure the presence of cancer cells in the specimen, immediately prior to snap freezing.

Note – these samples **must not** be used to provide paraffin-embedded tissue for determination of the subject's *c-MET*-amplification status. See instead Section 5.9.1.

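### Exclusion items 2 to 4 do not fit together: the Grade 1 recovery rule leaves out toxicity from the most recent therapy that the washout allows

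*Combined protocol and SAP*

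**What the plan says.** Three exclusion items in Section 4.3, repeated in the synopsis, govern prior therapy.

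- **Item 2** excludes on this condition: "The subject has received an investigational drug within 14 days of the first dose of study drug".
- **Item 3** sets the same 14 days for chemotherapy, immunotherapy, and radiation to at least 25% of the bone marrow. It sets a longer interval for a subject who "has received nitrosoureas or mitomycin C within 6 weeks prior to the scheduled first dose of GSK1363089". Both intervals count back from the scheduled first dose.
- **Item 4** is the only graded recovery rule. In Section 4.3 it reads "The subject has AEs due to investigational drugs or other medications administered more than 21 days prior to enrollment that have not recovered" to Grade 1 or better by CTCAE v3.0, alopecia excepted. It counts back from enrollment.

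The synopsis version of item 4 names different causes. It covers AEs "due to investigational drugs or anti-cancer therapy administered more than 21 days prior to enrollment that have not recovered". Both versions are current text.

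Section 5.9.2 requires the baseline biopsy to be taken "at least 14 days after the completion of any prior anti-cancer therapy". That sets a time interval and does not ask for recovery.

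**The concern.** A recovery rule normally matters most for those treated most recently. Here it applies only to subjects whose causal therapy is more than 21 days old, while the washout lets most subjects in after 14 days. Of two subjects with the same Grade 3 diarrhea, item 4 excludes the one treated 22 days before enrollment and does not exclude the one treated 16 days before.

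Safety and tolerability is a primary objective (Section 2). The study is open-label, non-randomized and without a comparator, so no control group can separate carried-over toxicity from drug effect. Section 5.11 lists fatigue, diarrhea, nausea and vomiting among the events attributed to GSK1363089, and recent chemotherapy could plausibly leave the same symptoms behind. If such a symptom worsens after Day 1, it counts as treatment-emergent and may be attributed to the study drug. There is also a subject-protection aspect: a new agent may be started before earlier toxicity has settled.

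**Working it through.** The plan states no figure for this point, so the check is interval arithmetic on its own windows.

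**Inputs.** Let t be the days from the causal prior therapy to first dose, and k the days from enrollment to first dose.

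- Washout (items 2 and 3): entry is allowed when t > 14. Day 14 itself is ambiguous in the wording, so day 15 is the first clearly eligible day.
- Washout for nitrosoureas and mitomycin C: t > 42.
- Recovery rule (item 4): it applies only when t − k > 21.

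**Uncovered interval.** Therapy passes the washout and escapes the recovery rule when 14 < t ≤ 21 + k. Its length is (21 + k) − 14 = 7 + k days.

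The documents do not state k, so it is an assumption:

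| k (days) | uncovered days before first dose | length |
|---|---|---|
| 0 | 15 to 21 | 7 |
| 3 | 15 to 24 | 10 |
| 7 | 15 to 28 | 14 |
| 14 | 15 to 35 | 21 |

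For nitrosoureas and mitomycin C the interval is 42 < t ≤ 21 + k, which is empty unless k > 21.

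**Does another criterion close the gap?**

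- Inclusion 9 limits neutrophils, platelets, hemoglobin, bilirubin, creatinine and ALT/AST whatever the date of prior therapy. The main hematologic, hepatic and renal laboratory toxicities are therefore covered.
- ECOG status of 2 or less, ability to take capsules, and the ACTH and QTc criteria also apply at any timing. None of them grades recovery from diarrhea, nausea, vomiting or fatigue.
- Exclusion 6 concerns uncontrolled intercurrent illness and is not a toxicity-recovery rule.

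**Does the analysis absorb it?** Section 8.1.4 counts an event ongoing at first dose as treatment-emergent only if it worsens, so stable carry-over is left out of the tables. Fluctuating carry-over is not. The rule also needs a baseline grade. Appendix A schedules no adverse-event collection at screening or baseline, and Section 5.3.1.3 lists it after the Day 1 dose. Medical history is taken at screening, but the documents do not say that it is graded.

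**Causal wording.** The synopsis says anti-cancer therapy, which includes radiation. Section 4.3 says other medications. Radiation is not clearly a medication, while any unrelated drug is, so the body text is narrower in one direction and wider in the other.

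**The case against.** The strongest reply is that the gap is narrow and largely contained. Much of this stands.

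- Item 4 turns on when the causal agent was given. Toxicity from an earlier cycle, more than 21 days back, is still caught. Only toxicity due solely to the latest treatment escapes.
- Inclusion 9 and the treatment-emergent definition limit the consequences, as shown above. The delay and reduction rule in Section 3.4 is triggered by toxicity of new onset, which stable carry-over would not meet. The causality scale in Section 7.1.1 lets investigators assign another cause.
- The documents do not explain the 21-day clause, so an unstated reason for it cannot be ruled out.

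A reader might also infer more than the documents support:

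- **That therapy as far back as Day −49 escapes (21 + 28).** This takes enrollment as the start of screening, because "Screening will be conducted within 28 days before initial treatment on Day 1". But Sections 5.2 and 5.6.6.1 place cardiac imaging, where indicated, before the decision to enroll, and Section 5.6.5 places eye counseling before enrollment. Enrollment therefore follows screening evaluations, and the full 28-day lag is not supported.
- **That any Grade 2 to 4 toxicity may enter.** Inclusion 9 rules this out for the main laboratory toxicities. Nor is a subject in the gap necessarily eligible. The subject is only not excluded by item 4.
- **That the Section 5.11 rates (fatigue 25%, diarrhea 21%, nausea 18%, vomiting 14%) size the problem.** They are rates of events considered drug-related. They do not show how many entrants were recently treated or carried toxicity.
- **That the response-rate test is undermined.** The definition of response and the decision rule in Sections 8.1.2 and 8.2 do not depend on item 4.

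None of this closes the gap for recent non-laboratory toxicity, because investigator discretion is not a criterion.

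**Conclusion.** The point holds as an eligibility inconsistency with a bounded effect on the primary safety objective. On the literal wording, non-laboratory toxicity due solely to therapy about 15 to 21 days before enrollment escapes the recovery requirement that applies to older therapy. The gap is at least 7 days, reached when enrollment and first dose coincide, and it grows by one day for each day between them. That lag is undefined, so the larger values in the table are illustrations. Nitrosoureas and mitomycin C fall outside the gap unless the lag exceeds 21 days. The number of subjects affected and the shift in adverse-event rates cannot be derived from the documents. Separately, the two versions of item 4 disagree on which causes count. Correction before further enrollment is worthwhile because it is cheap and bears on both subject protection and attribution.

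**What to change.** Reconcile items 2 to 4 in Section 4.3 and in the synopsis:

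1. Word them so that the washout and the existing Grade 1 recovery requirement cover the same subjects, or state why the most recently treated are exempt.
2. Count both from the same anchor, either enrollment or first dose. If enrollment is kept, define it.
3. Use one causal phrase in both places, and make clear whether radiation toxicity and AEs from non-cancer drugs are included.

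The sponsor's clinicians choose the interval; none is proposed here. The main change is one sentence in two places of an amendment, with matching edits to items 2 and 3 if the anchor changes. No analysis or sample-size change is needed. The downside is that some recently treated subjects may start later. The documents do not allow their number to be estimated.

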### 4.4. Concomitant Medication and Treatment

If the subject must use a concomitant medication during the study, it is the responsibility of the principal investigator (PI) to ensure that details regarding the medication are recorded on the CRF.

